### Sigh test

To explore the possibility of implementing predictive enrichment in a larger future RCT [17], we planned a pre-randomization test to assess the prevalence of patients with AHRF with improved oxygenation after the introduction of sigh. After enrollment, FiO_2_ will be titrated to obtain pulse arterial oxygen saturation (SpO_2_) of 90–96% maintaining clinical PSV settings including PEEP; then, all patients will undergo a clinical test of PSV + sigh to assess the prevalence of improved oxygenation in sigh responders vs. non-responders. To this end, we will first record the SpO_2_/FiO_2_ ratio at the start of the test; then, 30 min after the introduction of sigh as the cyclic pressure control phase set at 30 cmH_2_O for 3 s once per minute [14], SpO_2_/FiO_2_ will be collected again to quantify the number of patients in whom this ratio increased (i.e., “sigh responders”) [18]. To deliver sigh, ventilators will be switched to biphasic positive airway pressure mode with the lower pressure-level set at clinical PEEP and the higher pressure-level of the sigh set at 30 cmH_2_O with a 3-s inspiratory time and then a 57-s expiratory time [16].

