### Interventions: ventilation strategies for each study arm

#### PSV group

After randomization, clinicians will set PSV to meet the following targets: tidal volume (Vt) of 6–8 mL/kg of predicted body weight (PBW), with respiratory rate (RR) 20–35 bpm. FiO_2_ will be left as selected before the pre-randomization sigh test, while PEEP will be left as clinically set.

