#### Secondary endpoints

The study will also provide a preliminary evaluation of the safety of PSV + sigh by comparing the incidence of the following adverse events in the two study groups: hemodynamic instability with hypotension (i.e., SBP < 90 mmHg) despite vasoactive drugs; arrhythmias with heart rate < 40 or > 140 bpm; radiographic evidence of barotrauma (i.e., pneumothorax, pneumomediastinum, pneumatocoele or subcutaneous emphysema or new chest tube placement.

Furthermore, it will quantify the prevalence of short-term (i.e., within 30 min) and long-term (i.e., within 24 h in the PSV + sigh group) sigh responders defined by improved oxygenation. Finally, it will assess the following clinical outcomes: 28-day mortality; ventilator-free days; PSV level, PEEP value and oxygenation index on day 1–3; number of days on assisted ventilation until day 28; use of rescue treatments; number of quadrants involved on chest x-ray on day 1–5; ICU and hospital length of stay and tracheostomies. The listed variables will be analyzed by comparing the two study groups considering, first, the whole study population and, then, only patients who improved oxygenation during the pre-randomization sigh test (sigh responders).

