### Data collection

At enrollment, before the sigh test we will anonymously collect patients’ demographic information (e.g., age, sex, height, weight), past (e.g., hypertension, chronic medications) and recent (e.g., etiology of the acute respiratory failure, days since intubation) medical history, severity of lung injury (e.g., ventilation setting, arterial blood gases, respiratory system compliance, diagnosis of acute respiratory distress syndrome (ARDS)) and of systemic involvement (e.g., presence of shock, number of organ failures) and finally, ventilation data (e.g., RR, Vt, PEEP, FiO_2_, PSV level).

In both groups, for the first 24 h, we will assess the SpO_2_/FiO_2_ ratio, RR and PSV tidal volume every 4 h to further characterize physiologic response to sigh over time.

From day 1 (i.e., within 24 h from randomization) to day 28 or death or discharge from the ICU, the following data will be collected every day between 6:00 and 10:00 in the morning: arterial SpO_2_, arterial and central venous blood gas analyses, ventilation settings and pattern (i.e., sigh pressure level, sigh tidal volume, PSV level, PSV tidal volume, respiratory rate, PEEP, FiO_2_, minute ventilation, P0.1, mean airway pressure), heart rate, arterial blood pressure, central venous pressure, cumulative fluid balance, patient’s comfort assessed using a visual analog scale (VAS), RASS value, SOFA score and dosage of sedative agents and vaso-active drugs.

Moreover, each day we will collect information on use of rescue treatments (i.e., recruitment manoeuvers, use of PEEP ≥ 15 cmH_2_O, prone positioning, inhaled nitric oxide, extracorporeal membrane oxygenation), tracheostomy, switch from the allocated treatment to the other study arm for ≥ 24 h, switch to controlled ventilation for ≥ 24 h, reason for switch to controlled ventilation, adverse events (i.e., hemodynamic instability with hypotension with SBP < 90 mmHg despite vasoactive drugs; arrhythmias; radiographic evidence of barotrauma with pneumothorax, pneumomediastinum, pneumatocoele, or subcutaneous emphysema), SBT performance and reason for SBT failure, extubation or separation from mechanical ventilation, reintubation and reason for reintubation with time. We will collect data on day 28 for all enrolled patients on mortality, extubation that occurred outside the ICU and readmission to ICU.

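### The sigh-responder label counts any rise in SpO2/FiO2, so measurement variation alone makes responders of some unchanged patients and misstates the prevalence

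*Protocol article*

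**What the plan says.** The Sigh test section puts every patient through the test before randomization: "all patients will undergo a clinical test of PSV + sigh". Before it starts, "FiO_2_ will be titrated to obtain pulse arterial oxygen saturation (SpO_2_) of 90–96% maintaining clinical PSV settings including PEEP". The measurement rule has two steps. At baseline, "we will first record the SpO_2_/FiO_2_ ratio at the start of the test". The second value comes "30 min after the introduction of sigh as the cyclic pressure control phase set at 30 cmH_2_O for 3 s once per minute", when "SpO_2_/FiO_2_ will be collected again to quantify the number of patients in whom this ratio increased". Those patients are the sigh responders. The stated purpose is to explore predictive enrichment for a larger trial.

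Secondary endpoints repeats the idea without a threshold and adds "long-term (i.e., within 24 h in the PSV + sigh group) sigh responders defined by improved oxygenation". It also plans to analyse the listed secondary variables a second time in short-term responders only. Data collection states that, in both groups, "for the first 24 h, we will assess the SpO_2_/FiO_2_ ratio, RR and PSV tidal volume every 4 h".

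**The concern.** The rule is complete as written, and its cut-point is zero. If FiO2 does not change during the test, the ratio moves only with SpO2, so one displayed point decides the label. For example, 93% to 94% at FiO2 0.4 moves the ratio from 232.5 to 235 and makes a responder. Nothing separates an effect of sigh from ordinary variation or drift over 30 min, since no patient is observed without sigh in that window.

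Two outputs depend on the label: the prevalence intended to inform enrichment of the next trial, and the repeat of the secondary analyses in responders. If the label contains many unchanged patients, the first is misstated and the second is diluted.

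**Working it through.** **The plan's own figure.** The only computed figure in the article is the sample size. With failure rates of 22% and 15%, a 5% margin, one-sided alpha 0.05 and power 0.80: (0.22×0.78 + 0.15×0.85) × (1.645 + 0.842)² / (0.05 + 0.07)² = 128.4, so 129 per arm. It reproduces and does not depend on the responder rule. No responder prevalence or measurement error is stated, so the rest is a sensitivity calculation.

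**Inputs.** From the document: any rise counts; one value is described at each time; baseline SpO2 is 90–96%, which leaves room to rise and to fall. Assumed: FiO2 constant during the test, SpO2 shown as a whole number, and independent normal error with SD s per reading. Constant FiO2 is an inference. FiO2 is titrated before the test, and afterwards "FiO_2_ will be left as selected before the pre-randomization sigh test", but the text does not say that it stays fixed during the test.

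**Patients with no true change.** By symmetry, P(labelled responder) = (1 − P(tie)) / 2. Simulation with true SpO2 uniform on 90–96% gives:

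| SD s (points) | P(tie) | Labelled responder |
|---|---|---|
| 0.25 | 0.719 | 14% |
| 0.5 | 0.486 | 26% |
| 0.75 | 0.351 | 32% |
| 1.0 | 0.271 | 36% |
| 1.5 | 0.184 | 41% |
| 2.0 | 0.140 | 43% |

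The limit is 50% when ties vanish. One third is reached at s of about 0.8.

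**Effect on prevalence.** Observed = π × sensitivity + (1 − π) × false-positive rate, where π is the true prevalence. At s = 1 with a true gain of 2 points, sensitivity is 0.851 and the false-positive rate 0.364:
- π = 20%: 0.2×0.851 + 0.8×0.364 = 46%
- π = 40%: 0.4×0.851 + 0.6×0.364 = 56%
- π = 80%: 0.8×0.851 + 0.2×0.364 = 75%

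The direction reverses at π = FP / (1 − sensitivity + FP) = 0.364 / (0.149 + 0.364) = 71%. For a true gain of 1 point (sensitivity 0.636) the break-even is 50%. For 3 points (sensitivity 0.958) it is about 90%.

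**Effect on the responder subgroup.** In the 40% case, 0.6×0.364 = 0.218 of all patients are falsely labelled, out of 0.559 labelled. So 39% of the subgroup has no true response. If a treatment effect existed only in true responders, the subgroup would show about 61% of it.

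**What a threshold does.** A minimum rise of 2 points, for illustration only, labels 2.5%, 15% and 30% of unchanged patients at s = 0.5, 1 and 2. It also loses true gains. At s = 1, a patient with a true 2-point gain reaches the threshold whenever the error difference is zero or more, which has probability 1 − 0.364 = 64%, against 85% under the any-rise rule. With a 3-point gain it is 1 − 0.150 = 85%. A threshold therefore exchanges one error for another, which is the reason to put the continuous change first.

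**The case against.** Several points on the other side stand.

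- A reader might infer that a third or more of all patients become responders by chance. The percentages apply only to patients with no true change. With 30% true responders, false labels at s = 0.5 to 2 make up 0.7×0.26 = 18% to 0.7×0.43 = 30% of all patients. The SD is also not in the documents.
- A reader might infer that the prevalence must be inflated. It is overstated only below the break-even, and the true prevalence is unknown.
- A reader might take the 24 h wording to mean that any one 4-hourly reading above baseline makes a long-term responder. No text says so. The phrase parallels the 30 min one, which refers to one reading, and Data collection presents the 4-hourly values as describing response over time. After randomization FiO2 and PEEP are also adjusted (Adjusting ventilation settings), so a model of SpO2 noise alone does not describe the 24 h ratio. What remains is that the time of judgement is not named.
- A reader might treat the PSV arm's 4-hourly values as a clean measure of variation without sigh. They follow withdrawal of the test sigh, whose benefit the Discussion says disappears on stopping. They include FiO2 and PEEP changes, and they lie 4 h apart rather than 30 min.
- That each value is a single reading is inferred from the wording. The source cited for the definition and the full protocol are not shown.
- The test is exploratory, in a pilot trial. The label is fixed before randomization, so misclassification does not bias the comparison of arms within responders.

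None of this supplies a minimum rise. The article states the operative rule itself, and any increase satisfies it.

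**Conclusion.** The point holds in limited form. A zero cut-point with no comparison period without sigh will label some unchanged patients as responders. Their share is about 26% to 43% of unchanged patients for an assumed SD of 0.5 to 2 points, and 14% at 0.25. The observed prevalence is therefore not the true one, except near the break-even of about 50% to 90% at an SD of 1. The responder-only analyses lose contrast without gaining bias between arms. These sizes rest on constant FiO2, whole-number SpO2 and an SD that the documents do not give. The primary endpoint and the 258-patient sample size are unaffected. This is an inexpensive improvement to a secondary objective, worth making because that objective is meant to inform the next trial.

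**What to change.** Before the data are analysed:

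1. Make the continuous change in SpO2/FiO2 during the sigh test the main responder variable, both for describing response and for examining whether response modifies the treatment effect.
2. Also report responders by a minimum rise fixed in advance and larger than measurement repeatability, with its source stated, applied to the values already stored.
3. Keep any rise as a secondary description.
4. Name the single time at which long-term response is judged, for example the 24 h reading.

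The cost is wording and a little analysis. No new measurements are needed, and patients already enrolled can be handled the same way. The binary prevalence will depend on the threshold chosen, will probably be lower, and will miss some small true gains. The continuous change still cannot separate sigh from drift over 30 min, because the test has no period without sigh, and the report should say so.

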### Randomization

At the end of the sigh test, patients will be randomized through an online automatic centralized and computerized system to one of the two study groups (1:1 ratio): PSV or PSV + sigh. Due to the nature of the intervention, blinding will not be feasible.

### Interventions: ventilation strategies for each study arm

#### PSV group

After randomization, clinicians will set PSV to meet the following targets: tidal volume (Vt) of 6–8 mL/kg of predicted body weight (PBW), with respiratory rate (RR) 20–35 bpm. FiO_2_ will be left as selected before the pre-randomization sigh test, while PEEP will be left as clinically set.

#### PSV + sigh group

PSV will be set with the same protective targets of the PSV group (see above) but cyclic pressure control phase at 30 cmH_2_O for 3 s delivered once per minute (i.e., sigh) [14] will be added. FiO_2_ will be left as selected before the pre-randomization sigh test with clinical PEEP.

#### Adjusting ventilation settings

In both groups, PSV will be adjusted, at least every 8 h, as follows:PSV support will be decreased by 2 cmH_2_O if Vt > 8 mL/kg PBW and/or RR < 20PSV support will be increased by 2 cmH_2_O if Vt < 6 mL/kg PBW and/or RR > 35 and/or in the presence of respiratory distress (e.g., marked use of the accessory muscles)PEEP and then FiO_2_ will be increased by 2 cmH_2_O and 0.1 if SpO_2_ is < 90%FiO_2_ and then PEEP will be decreased by 0.1 and 2 cmH_2_O if SpO_2_ is > 96%.

The PSV group will be treated by protective PSV settings until day 28 or death or performance of a spontaneous breathing trial (SBT); the PSV + sigh group will be treated by protective PSV settings with the addition of sigh until day 28 or death or performance of a spontaneous breathing trial (SBT). Sigh settings will be left unchanged until day 28, death or the SBT.

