### Study population

Consecutive patients admitted with AHRF to each participating ICU, who have been intubated and switched to PSV between 1 and 7 days after intubation will be screened between 4 and 24 h from the start of PSV. Further inclusion criteria will be partial arterial pressure of oxygen (PaO_2_)/fraction of inspired oxygen (FiO_2_) ratio ≤ 300 mmHg (measured at clinical positive end-expiratory pressure (PEEP) and FiO_2_ values); clinical PEEP ≥ 5 cmH_2_O and stable Richmond Agitation-Sedation Scale (RASS) value of − 2 to 0. Exclusion criteria will be clinical PEEP ≥ 15 cmH_2_O; partial pressure of arterial carbon dioxide (PaCO_2_) > 60 mmHg; arterial pH < 7.30; PaO_2_/FiO_2_ ratio ≤ 100 mmHg (measured at clinical PEEP and FiO_2_ values); age < 18 years; presence of central nervous system or neuromuscular disorders; history of severe chronic obstructive pulmonary disease or fibrosis; AHRF fully explained by cardiac failure or fluid overload; evidence of active air leak from the lung (e.g., pneumothorax); cardiovascular instability (e.g., systolic blood pressure (SBP) < 90 mmHg despite vasopressors); clinical suspicion of elevated intracranial pressure; extracorporeal support; moribund status and refusal by the attending physician.

If an eligible patient is excluded from participation, the reason(s) for exclusion will be registered.

The Consolidated Standards of Reporting Trials (CONSORT) diagram of PROTECTION trial is presented in Fig. 2.

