#### Switch to controlled mechanical ventilation

In both groups, switch to protective controlled ventilation will be indicated if patient develops at least one of the following conditions: PSV support > 20 cmH_2_O; PEEP ≥ 15 cmH_2_O; unstable hemodynamic status (SBP < 90 mmHg with vasoactive drug); active cardiac ischemia (dynamic ST changes on cardiac monitor or electrocardiogram); unstable arrhythmias; uncontrolled hypertension (SBP > 180 mmHg); abrupt decrease in the level of consciousness (RASS <− 3); dangerous agitation (RASS > + 2); pH < 7.30; PaO_2_/FiO_2_ ratio ≤ 100 mmHg; necessity to perform diagnostic test (e.g., computed tomography (CT scan) or bronchoscopy).

Controlled ventilation will be set on volume mode with Vt 6–8 mL/kg PBW, RR to control pH, unchanged PEEP and FiO_2_. Controlled ventilation will be thereafter adjusted according to clinical evolution. Patients switched to controlled ventilation will be reassessed at least every 8 h and they will be switched back to PSV or PSV + sigh (to maintain study group assignment) targeting the aforementioned settings and adjustments as soon as all the following conditions are met: patient is able to trigger ventilator breaths; PaO_2_/FiO_2_ > 100 mmHg; PEEP < 15 cmH_2_O; pH ≥ 7.3; stable hemodynamic status with stable or decreasing doses of vasopressors for ≥ 6 h.

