#### Rescue therapies

In the case of desaturation (SpO_2_ ≤ 90%) it will be crucial to exclude hemodynamic impairment as a possible cause. Also, airway obstruction and ventilator malfunction must be ruled out. Provided those factors are excluded, a rescue step-up strategy will be allowed: institution of protective controlled mechanical ventilation (see above for settings) and performance of recruitment maneuvers at 40–50 cmH_2_O, PEEP ≥ 15 cmH_2_O, prone positioning and inhaled nitric oxide, extracorporeal membrane oxygenation. Patients undergoing controlled ventilation and rescue treatments will be reassessed at least every 8 h and switched back to PSV or PSV + sigh (to maintain study group assignment) with the aforementioned settings and adjustments as soon as all the following conditions are met: patient can trigger ventilator breaths; PaO_2_/FiO_2_ > 100 mmHg; PEEP < 15 cmH_2_O; pH ≥ 7.3 and stable hemodynamic status with stable or decreasing doses of vasopressors for ≥ 6 h.

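### The rules for resuming sigh do not require that no active air leak is present, and none provides for suspending sigh when one develops

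*Protocol article*

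**What the plan says.** All references are to the Protocol article.

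- **Entry.** Study population lists as an exclusion "evidence of active air leak from the lung (e.g., pneumothorax".
- **Dose.** In PSV + sigh group, a pressure-control phase at 30 cmH2O "for 3 s delivered once per minute (i.e., sigh) [14] will be added".
- **Duration.** Adjusting ventilation settings states that "the PSV + sigh group will be treated by protective PSV settings with the addition of sigh until day 28 or death"; the sentence then adds the SBT as a third stopping point. It also states: "Sigh settings will be left unchanged until day 28, death or the SBT".
- **Return after controlled ventilation.** Under Switch to controlled mechanical ventilation, once five conditions hold, "they will be switched back to PSV or PSV + sigh (to maintain study group assignment".
- **Rescue for desaturation.** Rescue therapies first asks that hemodynamic impairment be excluded, then says: "Also, airway obstruction and ventilator malfunction must be ruled out". It continues: "Provided those factors are excluded, a rescue step-up strategy will be allowed". Recruitment maneuvers at 40–50 cmH2O are among the steps. Patients are then "switched back to PSV or PSV + sigh (to maintain study group assignment) with the aforementioned settings and adjustments as soon as all" of the same five conditions are met.
- **Weaning.** The SBT section has three further returns to sigh: criteria not confirmed after the 60-minute sigh-free wait, a failed SBT, and renewed ventilation within 48 h.
- **Barotrauma as a harm.** Secondary endpoints compares radiographic barotrauma, including pneumothorax, between arms. The Discussion names pneumothorax among the potential adverse effects to be evaluated.

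**The concern.** The authors considered an active leak reason enough to keep a patient out, and they regard barotrauma as a possible harm of the intervention. Once a patient is randomised, no treatment rule uses that information. The return rules are directive: patients go back to the assigned arm when the listed conditions are met, and none of those conditions concerns the pleura. A patient with a persisting leak can therefore meet every written condition for restarting a 30 cmH2O inflation once a minute.

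What is at stake is the safety of individual patients and consistent handling across 23 centers. Recording the event as a safety outcome and reporting it to the coordinating center detects it, but does not tell the clinician what to do with sigh.

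**Working it through.** There is no plan figure to reproduce on this point; the check is a reading of every rule that continues, stops or restarts sigh.

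**Step 1. Look for air leak in each list.**

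| Section | What is listed | Items | Air leak named? |
|---|---|---|---|
| Adjusting ventilation settings | Inputs to the review at least every 8 h: tidal volume, respiratory rate, respiratory distress, SpO2 | 4 | No |
| Switch to controlled mechanical ventilation | Triggers: support level, PEEP, hemodynamics, ischemia, arrhythmia, hypertension, low RASS, high RASS, pH, PaO2/FiO2, diagnostic test | 11 | No |
| Same section and Rescue therapies | Return conditions: triggering, PaO2/FiO2, PEEP, pH, hemodynamics | 5 | No |
| Rescue therapies | Causes to exclude: hemodynamic impairment, airway obstruction, ventilator malfunction | 3 | No |
| SBT | Further returns to sigh | 3 | No |

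These rows show one omission in several places. They are not five separate faults.

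**Step 2. Compare with the other safety events.** Secondary endpoints names three kinds: hypotension despite vasoactive drugs, arrhythmia and barotrauma. The first two have counterparts among the switch triggers (unstable hemodynamics, unstable arrhythmias). Barotrauma has none.

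**Step 3. Which leaks do the existing rules catch?** A leak that produces SBP < 90 mmHg on vasoactive drugs, pH < 7.30 or PaO2/FiO2 ≤ 100 mmHg triggers controlled ventilation. So can the need for a diagnostic test such as CT. Two cases remain:

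- a stable leak that meets no trigger, for which the text continues sigh;
- a leak that led to a switch, or arose after one, and is still present when the five return conditions are met. The hemodynamic condition needs stable or falling vasopressor doses for at least 6 h, which can delay return but does not check for a leak.

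**Step 4. Exposure.** At one sigh per minute, uninterrupted: 1 × 60 × 8 = 480 sighs between reviews 8 h apart, and 1 × 60 × 24 = 1,440 in 24 h. These are upper bounds on dose. They say nothing about risk, and the article gives no air-leak rate from which to estimate the number affected.

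**Step 5. Effect on the design.** The sample size uses failure rates of 22% and 15%, a 5% tolerance, one-sided alpha 0.05 and power 0.80:

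n = (1.645 + 0.842)² × (0.22 × 0.78 + 0.15 × 0.85) / (0.05 + 0.07)² = 6.18 × 0.2991 / 0.0144 ≈ 128.4, so 129 per arm, as stated.

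No leak or sigh-exposure input enters. Suspending sigh is not among the failure criteria in Primary endpoint, so that definition is also untouched.

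**The case against.** The strongest objection is that this is a condensed article. Rules for suspending an intervention after an adverse event often sit in the full protocol, which is not shown and may contain one. That stands as a limit on the point. It does not remove it, because the article does more than stay silent: it sets out conditions and directs return to sigh when all are met.

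Several stronger readings are tempting, and the text does not support them.

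- *The plan forbids pausing sigh.* A reader might infer this from "Sigh settings will be left unchanged until day 28, death or the SBT". The natural meaning is that pressure, duration and rate are fixed. The listed stopping points are also not exhaustive, since the Abstract adds extubation and ICU discharge.
- *The lists bind clinicians in every respect.* The Discussion does say the protocol limits discretion, but only for decisions that might interfere with the primary outcome. It also describes the study as possibly largely pragmatic. Data collection records switches to the other arm lasting at least 24 h, so departures are foreseen.
- *Every entry exclusion must recur as a continuation rule.* PaCO2 > 60 mmHg and suspected raised intracranial pressure do not recur either. Air leak differs because the authors themselves link barotrauma to sigh.
- *Rescue compels recruitment maneuvers in a patient with pneumothorax.* The strategy is only allowed.

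It is also fair that plain PSV is not low-pressure by rule. Support up to 20 cmH2O with PEEP just below 15 cmH2O gives a set pressure just under 35 cmH2O in either arm. Withholding sigh removes one source of pressure, not all of them.

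**Conclusion.** The concern holds as a minor patient-safety improvement. The return rules direct resumption of PSV + sigh without requiring absence of an active air leak, the settings section gives no ground for suspending sigh when one develops, and the desaturation work-up omits pneumothorax. The gap is confined to stable leaks and to leaks that persist when the return conditions are met.

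A reader might infer that the plan exposes patients to a demonstrated harm. It does not show that: neither frequency nor added risk can be derived, and clinicians may already stop sigh on judgement. The point says nothing about a resolved, non-leaking pneumothorax. It assumes that the article's rules are those used at the bedside; if the full protocol has a rule for air leak, what remains is a difference in wording.

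**What to change.** 1. Adjusting ventilation settings: state that sigh is suspended if a new active air leak develops, that the patient continues protective PSV without sigh, and that the patient is analysed in the randomised group.
2. Switch to controlled mechanical ventilation, Rescue therapies and SBT: add absence of an active air leak to the conditions for resuming sigh.
3. Rescue therapies: add pneumothorax to the causes ruled out before rescue, in both arms.

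If the full protocol already contains such a rule, align the article with it instead.

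The cost is a short amendment. Ethics approval is sought per institution, and sixteen centers had approval and were recruiting according to Trial status, so it would go to each of those. A few patients in the PSV + sigh arm would receive slightly less sigh. Sample size and primary endpoint stay as they are.
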